### Objective

The authors will compare pCR rates and 3-year disease-free survival (DFS) rates as the primary endpoints between the two groups. pCR is defined no residual tumor or complete replacement of fibrosis in the surgical specimen (i.e. Mandard 1 or Dworak 4). 3-yr DFS is defined as proportion of the patients who survive without any local or distant recurrence/metastasis at the 3 years of follow up.

Secondary endpoints are radiotherapy-related toxicity, R0 resection rate, tumor response rate, surgery-related morbidity, and severity of peripheral neuropathy at 3 years. Acute and chronic toxicity will be recorded in the electronic case report form (eCRF). R0 resection rate is defined as the proportion of R0 resection among all TME specimens according to the pathologic results. TME quality evaluation will be performed by surgeons or pathologists: complete, nearly complete, and incomplete [30]. Tumor response rate is represented as grade of Mandard or Dworak [31, 32]. Postoperative complication within 30 days after TME will be recorded according to the grade of Clavien-Dindo classification of surgical complications [33]. Severity of peripheral neuropathy will be assessed at 3 years as well as every cycles of chemotherapy. The grade of any adverse event will be recorded by Common Terminology Criteria for Adverse Events (CTCAE) 4.0 [34]. Operative, pathologic, and chemotherapeutic reports are documented in the eCRF.

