Prolongation of the interval between CRT and TME has shown to increase pCR rates [11]. The interval has prolonged recently from 6 to 8 weeks up to 12 weeks, and several authors reported that extending the interval showed better pCR rates without increasing morbidity. [12–15] Another tries to achieve more pCR were adding platinum analogue (i.e. oxaliplatin) or vascular endothelial growth factor antagonist (i.e. bevacizumab) preoperatively and/or postoperatively based on 5-FU [16–18]. Unfortunately most of them failed to show higher pCR rates but increased acute toxicity [19, 20]. Recent trials reported that changing sequence of chemotherapy cycles as well as chemotherapeutic agents would attain better pCR rates, and new trials are launching. The examples are induction chemotherapy, consolidation chemotherapy, and sandwich regimen (prior to, concurrently with, and following radiation therapy) [21–26]. Sandwich regimen with capecitabine and oxaliplatin accompanied by 25 Gy of radiotherapy resulted in 42.2% of pCR rates, and even 10% of patients needed no surgery because the patients had achieved clinical complete response [22]. Garcia-Aguilar et al. reported that pCR rates were significantly increased in the patients who received various cycles of consolidation chemotherapy of FOLFOX regimen without significantly increased toxicity [21]. Then they showed that additional consolidation chemotherapy resulted in higher pCR rates in their multicenter, phase 2 trial [23]. However, it is not sufficient to conclude that consolidation chemotherapy is the only affecting factor to pCR due to several limitations. The interval and duration of consolidation chemotherapy were variable from 6 to 20 weeks. Moreover, adjuvant chemotherapy after TME followed by CRT was not standardized, and the total doses or cycles of chemotherapy was not consistent equally. Therefore, well-designed randomized controlled trials to assess the effect of consolidation chemotherapy alone after neoadjuvant chemoradiotherapy for locally advanced mid or low rectal cancer is required.

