All the patients who received CRT (50.4 Gy radiation with capecitabine 825 mg/m^2^ twice daily for 28 days) will be randomized in a 1:1 ratio into one of the following arms after screening: conventional chemotherapy group (control arm: Arm 1) or consolidation chemotherapy group (experimental arm: Arm 2) (Fig. 1). Stratification factors are age (< 70 or ≥ 70), clinical T stage (T1/2 or T3), and clinical N stage (N0 or N1/2). All eligible patients will be enrolled from approval of institutional review board (IRB) at each participating institution. The accrual period is 2 years and the follow up period is 3 years. The screening program includes history taking, physical examinations, laboratory tests, chest X-ray, EKG, and so on. If abnormal results requiring treatment were found within the screening, the patient will be given a proper treatment and the enrollment can be cancelled.

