**Fig. 1 Fig1:**
[figure not shown]
Flowdiagram of the trial

Arm 1 (conventional chemotherapy group): the patients, who are allocated to the arm 1, will undergo TME at 9 weeks after the CRT. They will receive 8 cycles of adjuvant chemotherapy with mFOLFOX6 (5-fluorouracil with Oxaliplatin) every 2 weeks within 6 weeks after TME. Arm 2 (consolidation chemotherapy group); the patients, who are allocated to the arm 2, will receive 3 cycles of mFOLFOX6 every 2 weeks after neoadjuvant CRT, and undergo TME at 9 weeks after the CRT. Then patients will receive the additional 5 cycles of adjuvant chemotherapy with mFOLFOX6 within 6 weeks after TME.

TME is intended to obtain a complete resection of the tumor (R0) with negative resection margins and adequate lymphadenectomy. The surgeon can decide stoma formation, medial-to-lateral or lateral-to-medial approach, vascular ligation (i.e. high tie or low tie), splenic flexure mobilization as well as the method of operation including open, laparoscopic, or robotic surgery. A complete resection (R0) or microscopic remnant resection (R1) should be confirmed by pathologists after TME. Patient with visible incomplete resection (R2) or distant metastasis is excluded in this study.

mFOLFOX6 regimen is composed of levoleucovorin (200 mg/m^2^) or leucovorin (400 mg/m^2^), oxaliplatin (85 mg/m^2^) for 2 h, then 5-FU (400 mg/m^2^) bolus followed by 5-FU (2400 mg/m^2^) for 46 h. All chemothrapy-related adverse events will be checked every cycle. Patients older than 70 years will receive chemotherapy as 75% reduced dose for the safety. [27–29] When the absolute neutrophil count decreased less than 1500/μl or any drug-related adverse effects of grade 3 were noted, dose reduction or delay of chemotherapy will be considered. However, delay of chemotherapy does not mean delay of TME in Arm 2. Even though a patient in Arm 2 lacks one or two cycles of consolidation chemotherapy due to chemotherapy-related adverse events, the patient will underwent TME at 9 weeks after CRT, and the data will be analyzed as intention-to-treat. All patients will equally visit every 3 months for 2 years, and then every 6 months for 3 years. Physical examination and laboratory test will be performed every 3 months, abdominal-pelvic CT scan every 6 months, chest CT every 1 year, and colonoscopy will be performed at 1 and 5 years to detect metastasis or recurrence.

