### Sample size calculation and randomization

Based on literatures, pCR rates and 3-year DFS after CRT for rectal cancer were known to be 10 to 28% and 50-65%, respectively [2, 6, 8–13]. Thus we hypothesize that the experimental arm would show a 15% improvement in pCR and in 3-year DFS, compared with the control arm (15 to 30% and 65 to 80%, respectively). The accrual period is 2 years and the follow-up period is 3 years. Based on the superiority design, one-sided proportion test and log-rank test with α-error of 0.025 and a power of 90% was conducted for both primary endpoints: pCR and 3-year DFS. The pCR of each group was considered to be 15 and 30%, and the 3-year DFS of each group was considered to be 65 and 80% assuming that accrual time was 2 years and follow up time was 3 years. Allowing neoadjuvant CRT for a drop-out rate of 10%, 358 patients (179 per arm) for pCR and 316 patients (158 per arm) for 3-year DFS will need to be recruited. Therefore a total of 358 participants (among 358 and 316) are needed. This study of 358 participants had at least 81% power (90% each = 0.9, so 0.9 × 0.9 = 0.81) to simultaneously detect a difference of pCR and 3-year DFS of two groups. Randomization will be performed in a 1:1 ratio by computer-generated random numbers, with the use of stratified permuted 4 blocks. It will stratified according to age (< 70 vs. ≥70), clinical T stage (T1/2 or T3), and clinical N stage (N0 or N1/2). Among 8 strata, 2 strata will not be used because clinical T1/2 N0 (age < 70 and ≥ 70) are not indicated for neoadjuvant CRT.

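### The 3-year DFS definition has no event for local failure before or at surgery, although patients are randomised before TME

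*Protocol article*

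**What the plan says.** All references are to the protocol article.

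- **Endpoint.** Under Objective, 3-year DFS is one of two primary endpoints, defined as the "proportion of the patients who survive without any local or distant recurrence/metastasis at the 3 years of follow up". The events are therefore death, local or distant recurrence, and metastasis.
- **Time of randomisation.** Under Study design, patients who have received CRT "will be randomized in a 1:1 ratio into one of the following arms after screening".
- **Surgery follows allocation in both arms.** Patients "who are allocated to the arm 1, will undergo TME at 9 weeks after the CRT". Those in Arm 2 "will receive 3 cycles of mFOLFOX6 every 2 weeks after neoadjuvant CRT, and undergo TME at 9 weeks after the CRT".
- **Exclusion.** The TME paragraph under Study design says: "Patient with visible incomplete resection (R2) or distant metastasis is excluded in this study".
- **Drop-out.** The Drop-out section lets a patient leave for unacceptable adverse events, a need for treatment outside the trial, refusal or pregnancy. It does not give such a patient a DFS status.
- **Analysis principle.** For Arm 2 patients who miss one or two consolidation cycles but still have TME at 9 weeks, Study design says "the data will be analyzed as intention-to-treat".

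**The concern.** Recurrence presupposes that disease was first cleared. In this trial the clearing operation comes after allocation. If the tumour grows locally before TME, or the primary is never removed, nothing has recurred. Read literally, the stated rule gives that patient no event until metastasis or death. If the operation leaves visible tumour, the patient is excluded. Either way a clear local failure is not recorded as a failure in a co-primary endpoint. The R0 resection rate does not fill the gap for unresected patients, because its denominator is TME specimens.

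The loss need not be equal between arms. Only Arm 2 receives chemotherapy between CRT and TME. Better control could bring more of its patients to resection, and toxicity could bring fewer. The consequence for the DFS comparison can go either way.

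**Working it through.** **1. The plan's own DFS sample size.** Inputs from the Sample size section: 65% vs 80%, one-sided 0.025, 90% power, 2 years' accrual, 3 years' follow-up, 10% drop-out ("one-sided proportion test and log-rank test with α-error of 0.025 and a power of 90% was conducted for both primary endpoints").

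- HR = ln 0.80 / ln 0.65 = 0.518.
- Events (Schoenfeld) = 4 × (1.960 + 1.282)² / (ln 0.518)² = 97.1, rounded up to 98.
- Event probability per arm with exponential times and uniform accrual = 1 − (e^(−3λ) − e^(−5λ)) / (2λ), where λ = −ln(S)/3. The mean over the two arms is 0.346.
- Patients = 98 / 0.346 / 2 = 142 per arm; 142 / 0.90 = 158 per arm, 316 in total.

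This matches the stated 316. The pCR size also reproduces: 161 per arm, 161 / 0.90 = 179, 358 in total. The arithmetic is sound; the issue is what counts as an event.

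**2. The definition against the patient pathway.**

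| Patient after randomisation | What the text provides |
|---|---|
| Local progression before TME, stays in the analysis | No event until metastasis or death |
| Primary never resected, stays in the analysis | No event until metastasis or death |
| Visible residual tumour (R2) or metastasis | Excluded |
| Needs other treatment, or refuses | May drop out; DFS status not stated |

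No row makes local failure before or at surgery a DFS event.

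**3. Possible size.** The article gives no rate, so the shares below are assumptions. Let q be the share of an arm that fails locally in this way and is alive and metastasis-free at 3 years. Let the remaining patients have the planned 65% and 80%.

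- Counted as failures: DFS = (1 − q) × S.
- Counted as disease-free: DFS = (1 − q) × S + q.
- The difference between arms therefore changes by q(experimental) − q(control).

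| q control / experimental | As failures | As disease-free | Change in gap |
|---|---|---|---|
| 5% / 2% | 61.75 vs 78.4, gap 16.65 | 66.75 vs 80.4, gap 13.65 | −3 points |
| 2% / 5% | 63.7 vs 76.0, gap 12.3 | 65.7 vs 81.0, gap 15.3 | +3 points |
| 5% / 5% | 61.75 vs 76.0, gap 14.25 | 66.75 vs 81.0, gap 14.25 | none; both levels 5 points higher |

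If these patients are removed instead, the measured gap is 80 − 65 = 15.0. Compared with counting them as failures, that is 15.0 − 16.65 = −1.65 points in the first row and 15.0 − 12.3 = +2.7 points in the second.

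**4. Other convention.** Suppose 65% and 80% already count these patients as failures. Scoring them disease-free then gives 65 + 5 = 70 vs 80 + 2 = 82 (gap 12), or 65 + 2 = 67 vs 80 + 5 = 85 (gap 18). The measured gaps differ from those in step 3, but the shift is again 3 points.

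**The case against.** The strongest reply is that the article does not say an unresected patient counts as disease-free. Its explicit rules point towards removal: R2 and metastatic patients are excluded, and a patient who needs other treatment or refuses may drop out. **This stands in part.** A reader might infer that all the worst local failures are scored as successes. The documents do not support that, because many of these patients would leave the analysis. But removal does not turn a local failure into an event either, and the definition still misscores anyone who remains.

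A reader might also take the intention-to-treat sentence as proof that unresected patients stay in the DFS set. It does not reach that far: it is written for Arm 2 patients who miss cycles and still have TME.

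Nor does the Background's mention of patients spared surgery show that non-operation is expected here. That figure comes from a different regimen, and this protocol describes no non-operative pathway.

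It can further be said that an article leaves the full event list to the full protocol or analysis plan. For the time origin and dating rules that is fair. But the event definition and the randomisation point are both stated here, and they do not fit together. A site might record pre-operative progression as local recurrence, but nothing in the text tells it to.

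Finally, the size is assumed, and equal shares leave the difference unchanged. Both points are correct.

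**Conclusion.** The point holds as a mismatch between a stated co-primary endpoint and the stated time of randomisation. No local failure before or at surgery is a DFS event. Patients who remain are disease-free until metastasis or death, and the others are excluded or may drop out.

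The 3-year DFS difference can move by up to the between-arm difference in the affected share, in either direction. With assumed shares of 5% and 2% that is about 3 points, against the planned 15. It is an upper limit, because it needs every such patient to be alive and metastasis-free at 3 years. With equal shares only the DFS levels are affected.

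A reader might infer a known direction of bias or a definite loss of power. The documents support neither: they give no rate of non-resection or pre-operative progression, and they do not say whether the planning rates already count such patients as failures. The arithmetic concerns the 3-year proportion; the effect on the Cox comparison is not quantified.

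**What to change.** In Objective, define DFS from randomisation for all randomised patients. Count as events, each dated when documented:

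- local progression that precludes resection;
- no resection of the primary, with a stated rule for the event date;
- macroscopic residual (R2) disease at surgery;
- local or distant recurrence, metastasis, and death from any cause.

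Reconcile this with the R2/metastasis exclusion under Study design and with the Drop-out section, so that it is clear these patients stay in the DFS analysis and how their status is obtained. Report event types by arm.

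The change concerns scoring and the analysis set, not how patients are managed. It costs a definition change, a few more early events and slightly lower DFS in both arms. The eCRF must also capture the date of, and reason for, no resection. The article lists operative, pathologic and chemotherapy reports in the eCRF but does not show that these items are collected, so this should be checked.

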### Sample size calculation and randomization

Based on literatures, pCR rates and 3-year DFS after CRT for rectal cancer were known to be 10 to 28% and 50-65%, respectively [2, 6, 8–13]. Thus we hypothesize that the experimental arm would show a 15% improvement in pCR and in 3-year DFS, compared with the control arm (15 to 30% and 65 to 80%, respectively). The accrual period is 2 years and the follow-up period is 3 years. Based on the superiority design, one-sided proportion test and log-rank test with α-error of 0.025 and a power of 90% was conducted for both primary endpoints: pCR and 3-year DFS. The pCR of each group was considered to be 15 and 30%, and the 3-year DFS of each group was considered to be 65 and 80% assuming that accrual time was 2 years and follow up time was 3 years. Allowing neoadjuvant CRT for a drop-out rate of 10%, 358 patients (179 per arm) for pCR and 316 patients (158 per arm) for 3-year DFS will need to be recruited. Therefore a total of 358 participants (among 358 and 316) are needed. This study of 358 participants had at least 81% power (90% each = 0.9, so 0.9 × 0.9 = 0.81) to simultaneously detect a difference of pCR and 3-year DFS of two groups. Randomization will be performed in a 1:1 ratio by computer-generated random numbers, with the use of stratified permuted 4 blocks. It will stratified according to age (< 70 vs. ≥70), clinical T stage (T1/2 or T3), and clinical N stage (N0 or N1/2). Among 8 strata, 2 strata will not be used because clinical T1/2 N0 (age < 70 and ≥ 70) are not indicated for neoadjuvant CRT.

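### A single published block length of 4, in a trial whose arms are visibly different before surgery, lets anyone who sees a stratum's earlier allocations work out later ones

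*Protocol article*

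**What the plan says.** The section on sample size calculation and randomization states: "Randomization will be performed in a 1:1 ratio by computer-generated random numbers", "with the use of stratified permuted 4 blocks". The wording is loose, but a block length of 4 is its only sensible reading, and no other length is mentioned.

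The same section names three two-level stratification factors (age, clinical T stage, clinical N stage) and counts the cells: "Among 8 strata, 2 strata will not be used", which leaves six. Centre is not a factor, although the Study design section describes a trial at several sites: "All eligible patients will be enrolled from approval of institutional review board (IRB) at each participating institution".

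According to the treatment description after Fig. 1, Arm 2 patients "will receive 3 cycles of mFOLFOX6 every 2 weeks after neoadjuvant CRT, and undergo TME at 9 weeks after the CRT". Arm 1 has TME at the same 9 weeks with no chemotherapy in the interval. The article describes no blinding.

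**The concern.** Permuted blocks force the arms to balance at the end of each block, so the last places in a block are determined by the first ones. If the length is fixed and known, an observer who has seen the earlier allocations can read off the later ones. Here the length is in a public article, and treating staff necessarily learn the arm of each of their own patients.

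If a recruiter can foresee the next arm, the decision whether or when to enter a particular patient may be influenced by it. Selection of that kind at entry can bias both primary endpoints, pCR and 3-year DFS. Adjustment for age, cT and cN would not remove it if the selection used other prognostic information. This weakness lies in a stated design choice. It is not a detail that the article has left out.

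**Working it through.** **Inputs.** Ratio 1:1, block length 4, three binary stratification factors with two cells unused, and 358 patients: all from the section on sample size calculation and randomization. The number and size of centres are not given, so a site's share of its stratum, *s*, is an assumption.

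**The plan's own figure.** The article gives no predictability figure. Its sample size, used below only as a base, reproduces. For pCR of 15% against 30%, one-sided α 0.025 and 90% power:

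n = [1.960·√(2·0.225·0.775) + 1.2816·√(0.15·0.85 + 0.30·0.70)]² / 0.15² = 160.8, so 161 per arm

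161/0.9 = 178.9, so 179 per arm and 358 in total. Block length does not enter this calculation.

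**Strata.** 2 × 2 × 2 = 8, minus 2 unused = 6. If centre were a factor, the count would be 8 times the number of centres. As stated, each block runs across institutions.

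**Observer who sees the whole stratum and knows the length.** There are 6 equally likely orders of two A and two B.

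- Certain in advance: the 4th place always; the 3rd only if the first two are alike (2 of 6 orders = 1/3). Share = (1/3 + 1)/4 = 1/3. On 358 patients, 358/3 ≈ 119.
- Best guess correct, by place: 1/2, 2/3, 2/3, 1. The sum is 17/6, and (17/6)/4 = 17/24 = 70.8%.

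**Observer at one site with share *s* of the stratum, who also knows where blocks begin.** An allocation is certain only if both earlier patients in one arm of that block were the site's own.

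- 3rd place: (1/3)·s². 4th place: s². Averaged over four places: (s²/3 + s²)/4 = s²/3.

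The last column is a simulated simple rule for a site that does not know its position in the block: guess the opposite arm to its own previous patient in the stratum.

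| Assumed share *s* | Certain, s²/3 | Opposite-arm guess correct |
|---|---|---|
| 50% | 8.3% | about 59% |
| 30% | 3.0% | about 56% |
| 20% | 1.3% | about 54% |
| 10% | 0.3% | about 52% |

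A simulation of the certain share gave 8.4%, 3.1%, 1.3% and 0.3%, in agreement with the formula.

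**Randomly varied lengths, full-sight observer.** 400 lists of 60 patients were simulated (358/6 ≈ 60, the average stratum), with lengths drawn with equal chance. The observer knows which lengths are possible but not which one is in use. As a check, length 4 alone gave 33.2% certain and 70.9% correct, close to the exact values.

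- Lengths 4 and 6: about 5.6% certain, 69% correct.
- Lengths 4, 6 and 8: about 2.4% certain, 68% correct.

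The gain is almost all in the certain allocations.

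**The case against.** The strongest reply is that the one-third figure describes an observer whom the article does not place at any recruiting site. Blocks are shared across centres, and site staff see only their own patients. A site with a tenth of a stratum could be certain of about 0.3% of its allocations. This stands, and it sets the size of the point: one third is an upper limit, for someone such as a central coordinator who sees a whole stratum.

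A reader might infer more than the document supports in four ways:

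- **That staff see every allocation.** Nothing says that one site learns the allocations of another.
- **That lists are held by site.** The count of eight cells leaves no room for centre.
- **That enrolment can be withdrawn once the arm is foreseen.** The clause "the patient will be given a proper treatment and the enrollment can be cancelled" applies when screening finds an abnormality that needs treatment. Patients "will be randomized in a 1:1 ratio into one of the following arms after screening", so the clause is a safety step before allocation.
- **That recruiters could select on tumour response to chemoradiotherapy.** No response assessment before randomisation is described.

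How and when an allocation is released is a detail that an article may leave to the full protocol, so its absence is no finding.

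It can also be said that varying the length hardly lowers guess accuracy, and that a site with a small share has little certainty to lose. Both are true. Neither is a reason to keep a fixed length, because the change costs little and removes most of the certain allocations where exposure is greatest.

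**Conclusion.** The point holds as an avoidable weakness of a stated design choice. It is neither a contradiction nor an arithmetical error. One disclosed length of 4, with visibly different arms, makes 1/3 of allocations certain and 70.8% guessable for an observer with full sight of a stratum. For a single site the certain share is about s²/3, from about 8% at half the stratum to 0.3% at a tenth. Those shares are assumptions. The formula also assumes that the site knows where blocks begin and that patients arrive from sites independently, so the site figures lean towards overstating the exposure. Nothing in the article shows that any selection took place.

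**What to change.** For the allocations still to be made, replace the fixed block of 4 with randomly varied lengths, for example 4 and 6, within the same six strata. Keep the lengths out of any document that sites can read, and report them only after accrual closes.

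The cost is a regenerated list and one amended sentence. The sample size stays at 358. The largest possible imbalance within a stratum from an unfinished block rises from 2 patients (4/2) to 3 (6/2), which matters little except in small strata. For a full-sight observer, certain allocations fall from 33% to about 6% and best-guess accuracy from about 71% to about 69%.

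The Discussion dates the first enrolment to December 2016, and accrual is planned for 2 years, so the change reaches only the patients not yet randomised. The article does not say how many that is.
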